| Grade 3                                                                               | Maintain dose

Consider use of growth factors to avoid delay with subsequent cycles.     | Consider use of growth factors to avoid delay with subsequent cycles.

Hold until <math>\geq 1500/\text{mm}^3</math>. If recovery takes:

1 wk – maintain dose;
$\geq 2$ wks – ↓ one dose level |
| Grade 4                                                                               | ↓ one dose level.

Consider use of growth factors to avoid delay with subsequent cycles. | Consider use of growth factors to avoid delay with subsequent cycles.

Hold until <math>\geq 1500/\text{mm}^3</math>.
↓ one dose level.                                                               |
| Platelet count decreased:
Grade 2                                                  | Maintain dose                                                                                         | Hold until <math>\geq 75,000/\text{mm}^3</math>.
If recovery takes:
1-3 wks – maintain dose
$\geq 3$ wks – ↓ one dose level                                                                           |
| Grade 3,4                                                                                           | ↓ one dose level                                                                                      | Hold until <math>\geq 75,000/\text{mm}^3</math>. ↓ one dose level                                                                                                                                                     |
| GI:
Diarrhea ( despite optimal antidiarrheal management )
Grade 2 | Maintain dose                                                                                         | ↓ only 5-FU one dose level                                                                                                                                                                                                   |

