|------------------------------------------------------------------------------------------------------------------------------------------------------------------------------------------------------------------------------------------------------------------------------------------------------------------------------------------------------------------------------------------------------------------------------------------------------------------------------------------------------------------------------------------------------------------------------------------------------------------------------------------|----------------------------------------------------------------------------------------------------------------------------------------|---------------------------------------------------------------------------------------------------------------------------|
| 
 
• All dose modifications for mFOLFIRINOX are based on the dose level changes on Table 8.2.3.1.
 
• Dose modifications must be based on AEs that occurred during the cycle (column 2) and AEs present on the scheduled Day 1 of Cycles 2-12 (column 3).
 
• Refer to footnote 'a' for management of anemia.
 
• Modifications in dose levels apply to 5-fluorouracil, irinotecan, and oxaliplatin unless otherwise indicated; leucovorin doses remain unchanged.
 
• Dose modifications must be based on the AE requiring the greatest modification.
 
 |                                                                                                                                        |                                                                                                                           |

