| CTCAE v5.0
Adverse Event/Grade                                                                                                                                                                                                                                                                                                                                                                                                                                                                                                                                                                                                        | Modifications for AEs that occurred during a cycle but
RESOLVE PRIOR TO THE NEXT TREATMENT CYCLE
(See footnote b ) | Modifications for AEs that
REQUIRE A DELAY IN ADMINISTRATION OF THE TREATMENT CYCLE
(See footnote c ) |

|                                                                     |                                                                                                                                                      |                                                                                                                                                                                                                                                                                                                |
|---------------------------------------------------------------------|------------------------------------------------------------------------------------------------------------------------------------------------------|----------------------------------------------------------------------------------------------------------------------------------------------------------------------------------------------------------------------------------------------------------------------------------------------------------------|
| Neutrophil count decreased:                           |                                                                                                                                                      |                                                                                                                                                                                                                                                                                                                |

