| Grades 2 (ANC 1000-1500/mm  )                           | Reduce irinotecan one dose level
Consider use of growth factors to avoid delay with subsequent cycles.                                     | Consider use of growth factors to avoid delay with subsequent cycles.

Hold until <math>\geq 1500/\text{mm}^3</math>. If recovery takes: 1-2 wks – maintain dose <math>\geq 2</math> wks - ↓ one dose level                                                                                |
| Grade 3                                                             | Reduce irinotecan one dose level. Maintain dose level of other drugs
Consider use of growth factors to avoid delay with subsequent cycles. | Reduce irinotecan one dose level.
Consider use of growth factors to avoid delay with subsequent cycles.

Hold until $\geq 1500/\text{mm}^3$ .

For other drugs:

1 wk – maintain dose or ↓ one dose level at discretion of treating oncologist;
$\geq 2$ wks – ↓ one dose level |
| Grade 4                                                             | Reduce irinotecan one dose level. Maintain dose level of other drugs
Consider use of growth factors to avoid delay with subsequent cycles. | Reduce irinotecan two dose levels; reduce doses of other drugs by 1 dose level.
Consider use of growth factors to avoid delay with subsequent cycles.

Hold until $\geq 1500/\text{mm}^3$ .                                                                                                    |
| Platelet count decreased:                             |                                                                                                                                                      |                                                                                                                                                                                                                                                                                                                |

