| Grade 2                                                             | Reduce irinotecan one dose level. Maintain dose level of other drugs                                                                                 | Hold until <math>\geq 75,000/\text{mm}^3</math>.

If recovery takes: 1-3 wks – maintain dose or ↓ one dose level at discretion of treating oncologist                                                                                                                                             |
| Grade 3                                                             | Reduce irinotecan one dose level. Maintain dose level of other drugs                                                                                 | Hold until <math>\geq 75,000/\text{mm}^3</math>.

Reduce irinotecan one dose level. For other drugs ↓ one dose level                                                                                                                                                                              |
| Grade 4                                                             | Reduce irinotecan one dose level. ↓ one dose level of other drugs                                                                                    | Reduce irinotecan two dose levels; reduce doses of other drugs by 1 dose level.

Hold until <math>\geq 75,000/\text{mm}^3</math>.                                                                                                                                                                 |
| GI:                                                   |                                                                                                                                                      |                                                                                                                                                                                                                                                                                                                |

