| Diarrhea ( despite optimal antidiarrheal management ) |                                                                                                                                                      |                                                                                                                                                                                                                                                                                                                |
| Grade 2                                                             | ↓ irinotecan one dose level                                                                                                                          | ↓ 5-FU and irinotecan one dose level                                                                                                                                                                                                                                                                           |
| Grade 3                                                             | ↓ 5-FU, oxaliplatin, and irinotecan one dose level                                                                                                   | ↓ 5-FU, oxaliplatin, and irinotecan one dose level                                                                                                                                                                                                                                                             |

|                       |                                                                                         |                                                                                         |
|-----------------------|-----------------------------------------------------------------------------------------|-----------------------------------------------------------------------------------------|
| Grade 4               | ↓ 5-FU and oxaliplatin one dose level, irinotecan two dose levels                | Discontinue                                                                             |
| Mucositis oral |                                                                                         |                                                                                         |

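### Table 8.2.3.2, grade 2 neutrophils: read by the column headings, on-time recovery cuts irinotecan for good while a one-week delay does not, and recovery at exactly two weeks has two answers

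*Combined protocol and SAP*

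**What the plan says.** Table 8.2.3.2 has two action columns. Column 2 is headed for adverse events that occurred in a cycle but "RESOLVE PRIOR TO THE NEXT TREATMENT CYCLE"; column 3 is for events that delay the cycle. Footnote b defines resolved as grade 1 or less on Day 1 of the next scheduled cycle, so that treatment goes ahead without delay.

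For grade 2 neutrophils (ANC 1000–1500/mm³):

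- Column 2: "Reduce irinotecan one dose level", with no discretion stated.
- Column 3: hold until ANC is at least 1500/mm³, then "If recovery takes: 1-2 wks – maintain dose", and go down one dose level if recovery takes two weeks or more.

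Section 8.2.3 bars re-escalation of any reduced dose. The instructions above the table base modifications on events during the cycle (column 2) and also on "AEs present on the scheduled Day 1 of Cycles 2-12 (column 3"). The cycle range in that quote exceeds the eight planned cycles, which has no bearing on this point. Footnote c has counts checked weekly during a hold.

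Three other rows are relevant:

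- Grade 3 neutrophils, column 3, reduces irinotecan one level and gives the recovery-time rule for the other drugs only: "1 wk – maintain dose or ↓ one dose level at discretion of treating oncologist", and one level down at two weeks or more.
- Grade 2 platelets in the mFOLFIRINOX table requires an irinotecan cut in column 2 and allows, in column 3, "1-3 wks – maintain dose or ↓ one dose level at discretion of treating oncologist".
- In the mFOLFOX6 table (8.2.1.2), grade 2 neutrophils are maintained if resolved, maintained after one week, and reduced at two weeks or more. Grade 2 platelets there read "1-3 wks – maintain dose", then one level down at three weeks or more.

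**The concern.** A dose rule should not treat a slower recovery more leniently than a faster one. Read by its headings, the grade 2 neutrophil row does so for irinotecan: recovery by Day 1 brings a lasting cut, and failure to recover by Day 1 brings a hold followed by the unchanged dose. Separately, the bands for one to two weeks and for two weeks or more both contain two weeks, and weekly checks make that a day on which recovery will be recorded.

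Irinotecan is the drug that separates the experimental arm from control, so what is at stake is how consistently it is delivered across sites. Section 5.0, footnote 6, asks for a blood count with each cycle or per institutional standards. A grade 2 count on Day 1 itself causes a hold, so column 2 is triggered only where a count is drawn between Day 1 visits. Whether a patient takes the cut then depends partly on local laboratory practice. Section 13.4.3 compares dose intensity between arms, though it does not say by drug.

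**Working it through.** The plan gives no figure of its own on this point. The check is a comparison of cells followed by dose arithmetic.

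**Ordering of the irinotecan step.** Levels removed in each neutrophil and platelet row of Table 8.2.3.2, read by the headings, with a one-week delay in column 3:

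| Row | Resolves on time | One-week delay | Ordered? |
|---|---|---|---|
| Grade 2 neutrophils | 1 | 0 | No |
| Grade 2 platelets | 1 | 0 or 1 | Only if the oncologist reduces |
| Grade 3 neutrophils | 1 | 1 | Yes |
| Grade 3 platelets | 1 | 1 | Yes |
| Grade 4 neutrophils | 1 | 2 | Yes |
| Grade 4 platelets | 1 | 2 | Yes |

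One row is firmly inverted, one is inverted only through discretion, and four are in order.

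**Dose inputs.** Table 8.2.3.1, level 0 and level −1 in mg/m²: irinotecan 150 and 135, oxaliplatin 85 and 65, infusional 5-FU 2400 and 1920. Table 7.2.3: eight cycles over 16 weeks. Assumption: one event, no other modification, all eight cycles given.

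**Planned irinotecan:** 8 × 150 = 1200 mg/m².

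**On-time event:**

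- In cycle 1: 150 + 7 × 135 = 1095 mg/m², and 1095/1200 = 91.25%.
- In cycle 7: 7 × 150 + 135 = 1185 mg/m², and 1185/1200 = 98.75%.
- The other drugs stay at 100%.

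**One-week delay, by the headings:** 8 × 150 = 1200 mg/m² over 17 weeks instead of 16. Intensity is 16/17 = 94.1% for all drugs.

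**One-week delay after cycle 1, both columns applied:** 1095 mg/m², and 0.9125 × 16/17 = 85.9% intensity.

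By the headings, the single-event contrast in irinotecan intensity is therefore about 91% against 94%. One step is 15/150 = 10%, the same size as the dose-rounding allowance in Section 10.1.

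**Recovery at exactly two weeks after cycle 1.** The maintain band gives full doses. The reduce band applies to all three drugs, since the table instructions apply level changes to 5-FU, irinotecan and oxaliplatin unless stated otherwise:

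- Irinotecan: 1095 of 1200, or 91.25%.
- Oxaliplatin: 85 + 7 × 65 = 540 of 8 × 85 = 680, or 79%.
- 5-FU: 2400 + 7 × 1920 = 15840 of 8 × 2400 = 19200, or 82.5%.

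The mFOLFOX6 grade 2 platelet row has the same kind of overlap at three weeks.

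**The case against.** The strongest reply is that the instruction naming both columns makes the row workable. An event seen during the cycle and still present on Day 1 would take the irinotecan cut from column 2 and the recovery-time rule from column 3, so the delayed course would never keep more irinotecan than the resolved one. This reading is available and removes the inversion. It is not the natural one: the column 2 heading and footnote b confine that column to resolved events, and the greatest-modification instruction ranks adverse events, not columns. It leaves the two-week overlap untouched.

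A reader might go further and infer that the row fails on this reading too, because column 3's maintain rule could then never apply to irinotecan. The documents do not support that. A grade 2 count first found on Day 1 can be handled under column 3 alone, where maintain does cover irinotecan. Where a mid-cycle count has already cut irinotecan, the rule still governs the other drugs, which is the structure the grade 3 row spells out.

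A reader might also infer a conflict in the grade 2 diarrhea row, where the cell requires an irinotecan cut and footnote d leaves it to discretion after multiple episodes. That is not established. The row is limited to diarrhea persisting despite optimal antidiarrheal management and footnote d is not, so the two can be read together. No marker tying the footnote to that cell is visible in the available text.

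It is also fair to say that Section 8.2 calls these modifications recommended, with deviations documented, and that both grade 2 neutrophil cells suggest growth factors. This softens the effect but does not settle which instruction a site should follow.

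**Conclusion.** The point holds as a minor wording fault in the experimental arm's dose rules. By the column headings and footnote b, the grade 2 neutrophil row is inverted for irinotecan at a one-week delay; by the both-columns instruction it is not. The row is therefore inverted or ambiguous. The two-week overlap stands on any reading, as does the three-week overlap for mFOLFOX6 platelets. The mFOLFIRINOX grade 2 platelet row inverts only when the oncologist chooses to maintain.

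The size is small. One irinotecan step is 10%, and a single on-time event costs between 8.75% (cycle 1) and 1.25% (cycle 7) of the planned total. The larger single difference is at the two-week boundary, where oxaliplatin can be 100% or 79% of plan and 5-FU 100% or 82.5%. These figures assume one event and eight completed cycles. The documents give no frequency, so no average effect on the arm can be stated. Alpha, power and the analysis populations do not change.

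**What to change.** Make the grade 2 neutrophil row of Table 8.2.3.2 monotone. The documents do not show which cell was intended, so the sponsor's clinicians should choose:

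- **Option A:** set column 2 to maintain the dose, as Table 8.2.1.2 does for the same grade. For one cycle 1 event, irinotecan is then 100% of plan with on-time recovery and 94.1% in intensity with a one-week delay.
- **Option B:** give column 3 the grade 3 row's structure, reducing irinotecan one level and limiting the recovery-time rule to the other drugs. The same figures become 91.25% and 85.9%.

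A keeps more irinotecan; B is more cautious on toxicity.

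Under either option, set the bands to maintain at one week and one level down at two weeks or more (for the other drugs only under B). This matches the mFOLFOX6 grade 2 row and the two-week threshold in the grade 3 row. In the mFOLFOX6 grade 2 platelet row, assign three weeks to one band only.

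The administrative cost is a few table cells in the next amendment, with no added patients or data. The clinical cost should be stated when choosing: a two-week recovery after cycle 1 would then leave oxaliplatin at 79% and 5-FU at 82.5% of the planned total under both options.
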